### 3. INTRODUCTION AND RATIONALE

#### 3.1 Summary of current situation

In response to the break out and the spreading of classical drug-resistant plasmodium strains, the WHO recommends the use of artemisinin-based combination therapies (ACTs) in the treatment of uncomplicated malaria episodes.

New ACTs are entering the African market and will be used by the public health care system. Until now, these ACTs were prescribed to a limited number of patients and most of the time within strictly regulated clinical studies with patients meeting restrictive selection criteria. The collection of safety data and the risk evaluation based upon observational data are critical in order to evaluate the risk/benefit profile of a product through its life cycle and allow providing information on the best use of medicines. In addition, the impact of the introduction of a particular ACT in the public health care system on the evolution of its efficacy and on the malaria morbidity and mortality is unknown and is worth being investigated.

#### 3.2 Eurartesim®

Eurartesim® is a fixed-dose combination product composed of dihydroartemisinin (DHA) and piperaquine phosphate (PQP) for the oral treatment of uncomplicated *Plasmodium falciparum* malaria. Eurartesim® contains DHA, to which all malaria strains are susceptible and to which drug resistance has not been reported. The long-term efficacy of Eurartesim® is secured by the presence of PQP. PQP is a second anti-malarial compound with a different mechanism of action and much longer half-life. Eurartesim® appears to offer significant benefits over existing licensed malaria treatments and is in line with current WHO treatment policy recommendations.

Two pivotal trials on the efficacy of Eurartesim® on treatment of uncomplicated *Plasmodium falciparum* malaria have been conducted in Africa and Asia, showing a high rate (>95 %) of treatment success. The Eurartesim® registration dossier has been submitted to EMA authorities and it got a centralized marketing authorization.

Evaluating possible drug-related side effects in patients with malaria and treated in the endemic countries can be difficult. There is considerable overlap between treatment-related symptoms and signs, and those of malaria (such as fever, anaemia) and concomitant illnesses (such as viral infections and parasitic infestations). Other reported AEs have been headache, vomiting, abdominal pain, asthenia, and cough.

The potential for Eurartesim® to prolong the QTc interval was investigated in parallel groups of healthy volunteers co-administered with high (~1,000 Kcal) or low (~400 Kcal) fat/calorie meals or in fasting conditions. Compared to placebo, the maximum mean increases in QTcF following Eurartesim® administration were 45.2, 35.5 and 21.0 msec, respectively, on day 3. Such QTcF prolongation observed under fasting conditions lasted between 4 and 11 hours after last dosing on day 3; afterwards, the mean QTcF prolongation compared to placebo decreased to 11.8 msec at 24 hours and to 7.5 msec at 48 hours. No healthy subject dosed in fasting conditions showed a QTcF greater than 480 msec, or an increase over baseline greater than 60 msec. The number of subjects overpassing these thresholds were 3 and 10 out of 64, respectively, for the low fat/calorie condition and 3 and 14 out of 40 for the high fat/calorie

condition. No subject had a QTcF value greater than 500 msec in any of the dosing conditions.

More details about Eurartesim® can be found in the SmPC of the product.

DHA is very rapidly absorbed, the Tmax being about 1-2 hrs after single and multiple dosing. DHA bioavailability resulted higher in malaria patients than in healthy volunteers, possibly because malaria *per se* has an effect on DHA disposition, which may reflect malaria-associated impairment of hepatic function, causing an increase in DHA bioavailability (reduction of hepatic first pass effect) without affecting its apparent elimination half-life, which is absorption rate limited.

Piperaquine (PQ), a highly lipophilic compound, is slowly absorbed. In humans, it has a Tmax of about 4-5 hours after single and repeated dose. Due to its slow elimination, PQ accumulates in plasma with an accumulation factor of approximately 3 after the scheduled multiple dose treatment of three days. In healthy volunteers, PQ exposure is increased approximately 3-fold when administered with a high fat/high calorie meal. This effect is of clinical relevance because PQ is responsible for the effect of Eurartesim® on QT interval. Accordingly, Eurartesim® should be administered with water far away from meals.

DHA is principally converted to  $\alpha$ -DHA- $\beta$ -glucuronide ( $\alpha$ -DHA-G). Studies in human liver microsomes showed that DHA was metabolised by the UDP-glucuronosyltransferase (UGT1A9 and UGT2B7) to  $\alpha$ -DHA-G with no cytochrome P450-mediated metabolism. *In vitro* drug-drug interaction studies revealed that DHA is an inhibitor of CYP1A2, therefore there is the potential for DHA to increase plasma concentrations of CYP1A2 substrates.

The metabolism of PQ in humans has not been studied *in vivo*. *In vitro* metabolism studies demonstrated that PQ is poorly metabolized by human hepatocytes (about 85% of PQ remained after 2 hours incubation at 37°C). PQ was mainly metabolised by CYP3A4 and to a lesser extent by CYP2C9 and CYP2C19. PQ was found to be an inhibitor of CYP3A4 (also in a time-dependent way) and to a lesser extent of CYP2C19, while it stimulated the activity of CYP2E1. As a consequence, there is the potential for increasing plasma concentrations of CYP3A4 substrates and also for the increase of PQ plasma concentrations when Eurartesim® is concomitantly administered with CYP3A4 substrates and CYP3A4 inhibitors, respectively. The elimination half-life of DHA is approximately 1 hour. Data regarding DHA excretion in humans are scarce. However, it is reported in the literature that the excretion of unchanged drug in human urine and faeces is negligible for artemisinin derivatives.

The elimination half-life of PQ is around 22 days for adult patients and around 20 days for paediatric patients. *In vitro* metabolism studies demonstrated that PQ is poorly metabolized by human hepatocytes and its major metabolites were a carboxyl acid cleavage product and a mono-N-oxidated product.

Animal studies showed that radiolabelled PQ is excreted by the biliary route, while urinary excretion is negligible.

### 3.3 Malaria in Burkina Faso, Mozambique, Ghana and Tanzania

#### Ghana

Malaria is the leading cause of morbidity and mortality reported in health facilities in the Northern areas where Navrongo HDSS is located. **Malaria transmission occurs during most months of the year but there is a distinct seasonal pattern with the peak of**

transmission coinciding with the period of the major rains (May – October) and the dry season (November – April) seeing very low rates of malaria infection. Transmission has been estimated to be 418 infective bites per person per year. The main malaria vectors are *A. gambiaes.l* and *A. funestus* constituting about 94.3% of the vector population. The predominant parasite species is *P. falciparum* (accounting for more than 90% of all infections). *P. malariae* is seen in a small proportion of infections (less than 5%) and some mixed infections of *P. falciparum* and *P. malariae*. *P. ovale* is rarely seen and no *vivax* is seen. The incidence of clinical malaria also shows some seasonality with an incidence density of infection varying from five cases per person- year in the dry season to over seven cases per person-year in the wet season. In a just concluded study of malaria morbidity and mortality in a birth cohort of children in the district (n=2200), 38.9% of all admissions in this cohort was due to malaria with malaria accounting for 50.9% of all hospital visits made by cohort members (unpublished data).

In the middle belt of Ghana where the Kintampo HDSS is located, The parasite prevalence in children <10 years of age is >50% all year round and the incidence of clinical malaria among children less than 5 years is about 7 episodes per child per year. The main vectors for transmission of malaria are *Anopheles gambiae* and *A. funestus* and the transmission is perennial but peaks between April and October. The annual entomological inoculation rate was 269 infective bites per person per year in 2005. Malaria is diagnosed by clinical suspicion and confirmed with rapid diagnostic test or microscopy. The first line treatment for malaria is artesunate-amodiaquine or arthemether-lumefantrine for uncomplicated malaria and quinine for complicated malaria. Chemical shops are the first point of call during a child's febrile illness and use of traditional medicine and left over drugs at home is also common in the study area.

### **Tanzania**

Overall malaria is on decline in Tanzania. However, it is still a very important public health problem in some areas including INESS study sites. Community based cross sectional studies that were conducted of late suggest population level parasite prevalence of about 14% in Rufiji and 3% in Kilombero-Ulangu health and demographic surveillance system (HDSS) sites (*Results from INESS study*). The infection is largely caused by *Plasmodium falciparum* parasites that are transmitted by *A. gambiae*, *A. arabiensis* and *A. funestus* mosquitoes. Malaria transmission in these two HDSS sites is intense and perennial. However, the disease becomes most prevalent from February to September, during and immediately after long rains. The main control strategies in existence are case management with artemether-lumefantrine and use of insecticide treated nets (ITNs).

### **Burkina Faso**

Burkina Faso a landlocked country is located in the heart of Africa. It is composed into 13 administrative regions that includes 45 provinces. The Kossi province belongs to Mouhoun region and borders the Republic of Mali. Nouna is located 297 km Northwest from Ouagadougou, the capital of the country. The Kossi province corresponds geographically to the Nouna Health District area, which has a size of 7464,44 km^2 and a population of about 320,000 in 2009. The HDSS operating since 1992, entirely belongs to this area. The area is a dry orchard savannah, inhabited and mainly by subsistence farmers and cattle keepers of different ethnic groups. The short rainy season usually lasts from June to October. The dry

season includes 2 types: a dry, cold and dusty period (November to February) and a dry and very hot period (March to May)

The annual rainfall in this area varies between 500-1000 mm. Throughout the year, the minimum and maximum daily ambient temperatures are approximately 20°C and 40°C. Malaria is defined as holoendemic in the area with most transmission occurring during or shortly after the rainy season and 99% being attributed to *P. falciparum*. July to December is considered as the high malaria transmission season, while the period January to June is considered as a low transmission season. Access to malaria prevention has remained rather limited until very recently with only one quarter of households possessing ITNs in 2007, but this proportion is increased to 59% in 2010. Access to quality malaria treatment was and is difficult in this rural study area. Only 14.6% of malaria cases are diagnosed by microscopy (Unpublished data). Only 15% of children with malaria having received early ACT in 2010.

### **Mozambique**

The Manhica Health Research Center (CISM – Centro de Investigação em Saúde de Manhica), is located in Manhica district, Maputo province, southern Mozambique. CISM maintains in its study area a demographic surveillance system since 1996 that covers 84.000 inhabitants, of which 44% are younger than 15 years of age. The census and household information are updated every six months and all houses are geopositioned. It also runs a morbidity surveillance system at the Manhica District Hospital (HDM) and 5 health centers in the area. A standardized questionnaire is filled out for all visits to the outpatient clinic and admissions to hospital of children younger than 15 years, where demographic information, symptoms and signs of the current illness, results, diagnosis, treatment and outcome are recorded. In all children with fever (axillary temperature  $\geq 37.5^{\circ}\text{C}$ ) or history of fever in the previous 24 hours a finger prick is performed to measure hematocrit and prepare blood smears to determine parasitemia. Only children with a positive blood smear receive antimalarials, currently artemether plus lumefantrine (AL) for uncomplicated malaria. The study area covers around 500 km^2 and includes semi-rural and rural areas, where houses are typically made of cane walls with thatched or corrugated iron roofs. The population is of the Shangana-Ronga ethnic group and is mainly composed of subsistence farmers, petty traders and workers in a nearby sugar cane factory.

There are two distinct seasons: a warm and rainy season from November to April and a cool dry season the rest of the year. The transmission of malaria in the area is stable with seasonality, with *P. falciparum* being responsible for the majority of the cases and *A. funestus* being the main vector. Transmission, that used to be of moderate intensity, with an entomological inoculation rate of 38 infective bites/person/year in 2002, has decreased in the last few years. Malaria preventive measures in place in Manhica include diagnosis of malaria cases with blood smears or rapid diagnostic tests, treatment of confirmed cases with AL, the free distribution of LLINs to pregnant women through antenatal clinics, indoor residual spraying (IRS) with DDT and intermittent preventive treatment in pregnant women (IPTp) with three doses of sulfadoxine-pyrimethamine as indicated and provided by the NMCP.

In 2010 minimum community-based incidence rates of outpatient malaria cases per 1,000 child years at risk detected through the morbidity surveillance system ranged from 39-220 in

infants, 110-764 in children aged 1 to <5 years and 64-274 in children aged 5 to 15 years depending on the area. Malaria accounted for 7-34% of all outpatient visits in children younger than 15 years depending on the area. In community cross-sectional surveys in 2010 and 2011 the prevalence of parasitaemia was <15% for all age groups and areas.

### **3.4 Project rationale**

The project will take place within up to 7 HDSS centres located in four countries and it has a double interest. The first interest is to collect safety data in real conditions of use on a medicine the safety profile of which is well known only through classical clinical studies.

The second interest is to develop new methods for actively performing pharmacovigilance, which will subsequently be used for other anti-malarial drugs, and drugs in other therapeutical classes in sub-Saharan Africa.

This program is being implemented in close collaboration with the NMCP of each of the four countries and the Pharmacovigilance Department of the Sponsor or his/her Designee. The collected data will be regularly submitted to an independent committee in charge of safety monitoring, as well as to the Health Authorities and will be communicated to the WHO collaborating pharmacovigilance centre in Uppsala.

## **4. STUDY OBJECTIVES**

### **4.1 Primary objective**

The primary objective is the evaluation of the clinical safety of Eurartesim® in standard conditions of use (unsupervised treatment intake), on a population of approximately 10,000 patients with signs and symptoms of uncomplicated malaria confirmed by a parasitological diagnosis or, when this test is not available, by WHO diagnostic criteria.

This sample will allow the detection of rare adverse events (i.e. with an incidence of 1 case per 3,000 patients).

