To facilitate drug administration in small children, tablets will be crushed on a spoon and given with water. If vomiting occurs within 30 min from drug administration, dose will be re-administered. If vomiting occurs within 30 to 60 min, half a dose have to be re-administered. Re-dosing should not be attempted more than once. The first study drug administration will be supervised at the site in all the patients, instruction on the second and the third drug administration will be given to patients.

In the nested 1000 patient group, the second administration will be given preferably at the study site or at the patient's home by a trained CHA. If the dose is administered at home, a specific diary will be provided to the patient in which the CHA have to fill in the second drug administration data. This diary will be maintained by the patient and will be returned to the site when the third administration will be provided (at the site).

Eurartesim® will be provided free of charge by Sigma-Tau ifr S.p.A.

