All the patients will be instructed to refer to the CHA or the designated HF in the HDSS should any adverse event occur within the 28 day after the start of the Eurartesim® administration.

In addition the regional hospital will be alerted to check referrals for participation in the study, and there will be a collection on a regular basis of any data related to patients who are treated in regional hospitals who have taken part in the study.

The patients recruited in the 1,000 subset group will be reviewed at the HF on day 3 (last day of administration of Eurartesim® dose). Before the Eurartesim® administration, a blood sample will be collected for PQ concentration evaluation (in all the 1000 subgroup of patients) and a single ECG will be recorded. The last dose of Eurartesim® will be directly administered by the HA to the patient after documentation that the last meal was taken more than 3 hours prior to administration. Three to four hours after the Eurartesim® administration, a blood sample for haematology, blood chemistry and PQ concentration will be collected and a triplicate ECG will be recorded.

The following information will be recorded in the second part of the chart (in triplicate):

- The HA or study team staff will record his/her own 4 digit identification number (number of the health centre he/she is attached followed by a 2 digit number which will be assigned to him/her when the study starts).
- Date of the visit.
- Clinical condition (recovered status or continuation of the illnesses).

- Time of drug administration
- Compliance with the Eurartesim® treatment during the three day treatment.
- Results of the ECGs and laboratory examinations
- Occurrence of Adverse Events.

The patients recruited in the subset will have to come back at the health facility on day 7 to perform a further single ECG, a blood sample drawing for haematology and biochemistry determinations and to collect, if any, Adverse Events occurred.

Again the HA or study team staff will record his/her own 4 digit identification number and record the appropriate information on the patient chart.

All the patients will be instructed to refer to the CHA or the designated HF in the HDSS should any adverse event occur starting from the 7 day visit/contact and the 28 day after the start of the Eurartesim® administration.

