### **7.3 Patients who did not receive follow-up visits/contacts**

#### **7.3.1 Premature discontinuation before drug intake**

**In case a participant fulfils all selection criteria, he/she is enrolled in the study and is attributed an enrolment number/participant ID number. If for any reason, the participant cannot be given the study drug and must discontinue participation in the study, the reasons for this will be collected by the CHA or HF staff.**

**These particular subjects will not be part of the safety and efficacy analysis. Additional subjects will need to be recruited in the study in order to make up for the total of 10,000 (9,000 and 1,000) subjects needed for analysis.**

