### **9.2 Analysis in the whole sample**

#### **Analysis in the whole sample and in the Subset population**

The statistical analysis will be mainly descriptive. The estimates of the incidence of adverse events will be based on crude rates. All estimates will be complemented with appropriate 95% confidence intervals.

The adverse events shall be regularly coded using MedDRA before database lock.

All SAEs and AESIs will be reviewed centrally by an independent safety monitoring panel.

Incidences will be computed on the following classes of AEs, overall and by SOC/PT:

- All AEs
- Serious AEs
- Serious AEs related to study treatment
- AEs of special interest (AESIs)
- AEs which caused early discontinuation of Eurartesim®
- AEs related to Eurartesim® treatment

Specific analyses will be carried-out on the AESIs. Correlation analyses will be carried-out in order to verify if their occurrence is more frequent with the previous/concomitant use of other drugs (specific classes to be determined in the statistical analysis plan), including antimalarials, in presence of co-morbidity (specific classes to be determined in the statistical analysis plan), or in presence of parasitaemia.

Compliance will be computed in the whole population and in the subset of **about 1,000** patients, calculating for each patient the ratio between the number of tablets taken and the number of tablets that the patient should have taken. Two groups of patients shall be described: compliant = 100% treatment compliance and non compliant = other cases. The safety profile of compliant vs non-compliant patients will be compared.

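### Section 9.2 specifies no adverse event estimate for the usual-use main group, although the primary objective concerns unsupervised intake

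*Protocol*

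**What the plan says.** Section 4.1 defines the primary objective as clinical safety "in standard conditions of use (unsupervised treatment intake), on a population of approximately 10,000 patients". Section 7.3.1 shows how that number is made up: extra recruits are to "make up for the total of 10,000 (9,000 and 1,000) subjects needed for analysis". So 10% of the primary population is the nested group.

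**Dosing.** Section 5.3 states that "The first study drug administration will be supervised at the site in all the patients", and Section 7.2.2 repeats this for all 10,000. In the nested group "the second administration will be given preferably at the study site or at the patient's home by a trained CHA" (Section 5.3). The third nested dose is directly observed at the facility (Section 7.1) and is given "to the patient after documentation that the last meal was taken more than 3 hours prior to administration" (Section 7.2.3). It also follows a Day 3 pre-dose QTcF check (Section 5.1).

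**AE detection.** Nested patients are asked about AEs at Day 3 and Day 7 visits, with scheduled ECGs and laboratory tests (Section 5.1). Main-group patients have one contact around Day 5 (Section 7.2.3), and an ECG only when clinical signs suggest cardio-toxicity (Section 8.5). Both groups can report events up to Day 28.

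**Analysis.** In Section 9.2 the incidences of all AE classes, AEs of special interest (AESIs) included, come under the heading "Analysis in the whole sample and in the Subset population". The estimator is fixed: "The estimates of the incidence of adverse events will be based on crude rates". Neither an analysis restricted to the main group nor a breakdown by group is named.

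**The concern.** The objective describes one way of taking the drug, and the population assigned to it contains two. As planned, every nested dose is either supervised or given by staff. The patients closest to usual use are the main group, and they are the only group for which Section 9.2 names no estimate.

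Two things follow. First, a whole-sample AE rate mixes patients treated and questioned in different ways, so it is not a clean estimate for usual use. Food matters here, because Section 3.2 reports piperaquine exposure about three times higher with a high-fat meal, and documented fasting before the last dose is required only in the nested group. Second, some events will be found mainly by scheduled ECGs or laboratory tests, and only nested patients have these. Section 8.5 itself says that drug-induced QTc prolongation usually causes no symptoms. Dividing such events by the whole sample uses a denominator in which most patients had little chance of being found to have one.

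Section 4.1 also conflicts with Section 5.3 on wording. If dose 1 is supervised in everyone, then even main-group intake is unsupervised only for doses 2 and 3.

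**Working it through.** **Inputs from the protocol:** 9,000 main and 1,000 nested patients (7.3.1); a 0.95 probability of identifying events of incidence 1/3,000 in about 10,000 patients, and nested probabilities of 0.95 and 0.865 at incidences 0.003 and 0.002 (9.3).

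**Assumptions, not given in the protocol:** the ratio of recorded AE rates between the groups, and the loss to follow-up. Ranges are shown.

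**1. The plan's own figures.** P(at least one event) = 1 − (1 − p)^n.
- Whole sample: 1 − (1 − 1/3,000)^10,000 = 0.964, which supports the stated 0.95.
- Nested: 1 − 0.997^1,000 = 0.950 and 1 − 0.998^1,000 = 0.865. Both match.

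**2. General AEs.** The pooled rate is 0.9 × main rate + 0.1 × nested rate. With r = nested rate / main rate, pooled / main = 0.9 + 0.1r.

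| r | pooled / main | change |
|---|---|---|
| 0.5 | 0.95 | −5% |
| 1 | 1.00 | none |
| 3 | 1.20 | +20% |
| 5 | 1.40 | +40% |

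Closer questioning and testing push r above 1. Checked fasting and the Day 3 QTcF check could lower true risk and push it down. The protocol does not settle the net direction.

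**3. Events found mainly by scheduled ECG or laboratory tests.** With q = main rate / nested rate, pooled / nested = 0.1 + 0.9q. The dilution is the reciprocal.

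| q | pooled / nested | dilution |
|---|---|---|
| 0 | 0.100 | 10-fold |
| 0.25 | 0.325 | 3.1-fold |
| 0.5 | 0.550 | 1.8-fold |
| 1 | 1.000 | none |

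Example at q = 0: three such events in the nested group are 3/1,000 = 0.30% there, but 3/10,000 = 0.03% in the whole sample.

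**4. What the main group alone can support.**
- Precision: confidence interval width scales with 1/√n, and √(10,000/9,000) = 1.054, so intervals are about 5% wider.
- Rare events: 1 − (1 − 1/3,000)^9,000 = 0.950. The number needed for 0.95 is ln 0.05 / ln(1 − 1/3,000) = 8,986, which leaves a margin of 14 patients.

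| assumed loss | main group | pooled sample |
|---|---|---|
| none | 9,000: 0.950 | 10,000: 0.964 |
| 5% | 8,550: 0.942 | 9,500: 0.958 |
| 10% | 8,100: 0.933 | 9,000: 0.950 |

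Section 7.3.3 expects some loss to follow-up, and Section 7.3.1 replaces only patients who never received the drug.

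**The case against.** Much of the case on the other side stands.

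- **The nested rate is not lost.** Section 9.2 also computes every AE class in the subset, and it places the QTc and laboratory analyses there. The cardiac AESI calculation in Section 9.3 uses n = 1,000. A reader might infer that QT-related risk will be reported ten times too low. The documents do not support that: the subset rate appears as well, and the ten-fold figure needs no detection at all among 9,000 patients and every symptom-free nested finding recorded as an AESI. The protocol fixes neither.
- **General AE distortion is limited.** The nested weight is 10%, the study is mainly descriptive, and the sign is unknown. To say that the pooled rate is useless would go too far.
- **The group contrast can be overdrawn.** The three-hour food instruction applies to everyone (5.3), and the time of last food is noted at dose 1 in all patients (7.2.2). Home visits back up incomplete or unreliable main-group contacts, and hospital reports and spontaneous reports to Day 28 are collected in both groups (5.4, 7.2.3). A reader might also infer that the Day 1 ECG screens out nested patients with QTc above 450 ms. Section 6.2.2 lists that value under personal or family history for all patients, and no section says that the Day 1 ECG is used this way.
- **The main group can be recovered.** Whole-sample counts minus subset counts give it, and an analysis plan could add the table. The Summary speaks only of usual conditions.

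What remains is narrower. Section 4.1 names unsupervised intake, Section 9.2 names the populations for the incidence estimates, and the population that fits the objective is not among them. Leaving readers to subtract does not identify the usual-use estimate or give its confidence interval.

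**Conclusion.** The point holds as a mismatch between the objective and the populations analysed, and it is cheap to correct. It does not invalidate the study. No usual-use estimate is specified, and whole-sample rates of events found mainly by scheduled tests are hard to interpret.

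The size depends on ratios that the protocol does not give: −5% to +40% for general AEs over r = 0.5 to 5, and 1.8-fold to 3.1-fold dilution for test-detected events at main/nested ratios of 0.5 and 0.25, with ten-fold as the limit.

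A reader might conclude that the main group should simply replace the pooled sample throughout, because 9,000 patients still give 0.950. That holds only with almost no loss to follow-up, so the pooled sample should be kept for rare-event detection.

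**What to change.** 1. In Section 9.2, name AE incidence in the main group (about 9,000) as the usual-use estimate with its 95% confidence interval, and show the nested group separately.
2. For AEs and AESIs detected by scheduled ECG or laboratory tests, compute incidence with the nested denominator only.
3. Keep the pooled 10,000 for rare-event detection: clinically detected events, serious AEs and deaths. The 1/3,000 statement in Section 9.3 then keeps its allowance for loss to follow-up.
4. Reconcile the reference to unsupervised intake in Section 4.1 with Sections 5.3, 7.1, 7.2.2 and 7.2.3, so that the objective describes how doses are taken in each group. This concerns the wording of the objective and implies no change to dosing.

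**Cost.** The data are already to be collected, so the change is to text and tables. Main-group intervals are about 5% wider than pooled ones. The main group alone has a 0.950 probability of showing a 1/3,000 event with no loss, and about 0.94 with an assumed 5% loss, which is why item 3 keeps the pooled sample for that purpose.
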